**University of Auckland**

**[name] PhD**

**Department of Biochemistry**

**University of Otago**

The genome-wide association studies (GWAS) of serum urate and fractional excretion of uric acid (FEUA) have consistently reported a strong association with common variants of *SLC2A9* and *ABCG2* [4-8]. The Genetics of Gout in Aotearoa study has strongly implicated the *SLC2A9* gene in development of gout in Māori and Pacific people (odds ratios  $\geq 5.0$ ) [9]. Variation in the *rs11942223* *SLC2A9* single nucleotide polymorphisms (SNP) was most strongly associated with gout in Māori, Pacific and Caucasian case-control cohorts in this study. Between 31.7%-47.2% of control participants possessed at least one protective alleles (i.e. 1/2 and 2/2 genotypes)

*ABCG2* encodes the cellular efflux pump breast cancer resistance protein (BCRP). An *ABCG2* variant (*rs2231142*, *Q141K*) is strongly associated with gout and hyperuricaemia, and is thought to regulate serum urate concentrations through extra-renal (gut) underexcretion [10]. In addition, *ABCG2* variants play a role in treatment responses to allopurinol (a purine xanthine oxidase inhibitor), and BCRP can transport allopurinol [11].

Our recent studies of acute fructose loading have shown that *SLC2A9* and *ABCG2* variants influence changes in serum urate, serum glucose changes and fractional excretion of uric acid (FEUA) in response to a fructose load [12, 13]. It is unknown whether these effects occur due to direct interactions with fructose, or whether these effects are non-specific responses to hyperuricaemia induced by fructose. Here, we aim to examine the role of *SLC2A9* and *ABCG2* variants on serum urate responses and renal urate handling in response to an acute inosine load.

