## **9. STATISTICAL CONSIDERATIONS**

### **9.1. Justification of Sample Size and Study Population**

We plan to recruit 100 healthy subjects without documented gout; 50 participants of Māori or Pacific ancestry and 50 participants of Caucasian ancestry. We have chosen to pool Māori and Pacific participants into a single group of Polynesian ancestry, as the allele frequencies for *SLC2A9* are very similar in these two groups, and our previous data also indicate similar renal responses to hyperuricaemia in Māori and Pacific participants [13]. Sample size calculations have been based on the variability of change in serum urate at each time point in our previous study of fructose induced hyperuricaemia [13] and an analysis of inosine use for Parkinson's disease [1]. We have selected the *SLC2A9* SNP *rs11942223* for the primary analysis, and assume that approximately 30% of participants will have the protective allele based on our previous work in the Genetics of Gout in Aotearoa study [9]. The variability in the change in serum urate to fructose load [13] was consistent within groups with and without protective alleles across all time points (SD 0.03 mmol/l). With 70 participants without the protective allele and 30 with the protective allele the proposed study is adequately powered (90% at the 5% significance level for a two tailed test) to detect a difference in the change in serum urate between these groups of at least 0.02mmol/l.

We wish to perform a subgroup analysis using Māori or Pacific and Caucasian case-control cohorts, and have powered the study based on the above assumptions. Here we will recruit 50 participants of each ancestry, and estimate that 14-16 participants within each ancestral group will have the protective allele. In the smallest group comparison, n=16 vs. n=34 within an ancestral subgroup, there is in excess of 90% power (at the 5% significance level for a two tailed test) to detect a difference in the change in serum urate 180 minutes after an oral inosine challenge of at least 0.03 mmol/l. Pooled factorial secondary analyses will therefore similarly be adequately powered for the same effect size.

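### Section 9.1 calls 16 vs 34 the smallest subgroup comparison although its own 14-16 carrier range goes down to 14 vs 36, where power for 0.03 mmol/l is about 88%, not above 90%

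*Protocol*

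**What the plan says.** Protocol section 9.1 plans 50 participants in each of two ancestral groups. For the subgroup analysis the authors "estimate that 14-16 participants within each ancestral group will have the protective allele". The next sentence reads "In the smallest group comparison, n=16 vs. n=34 within an ancestral subgroup, there is in excess of 90% power", at the two-sided 5% level, "to detect a difference in the change in serum urate 180 minutes after an oral inosine challenge of at least 0.03 mmol/l". The SD comes from the earlier fructose study, where variability "was consistent within groups with and without protective alleles across all time points (SD 0.03 mmol/l"). The paragraph ends: "Pooled factorial secondary analyses will therefore similarly be adequately powered for the same effect size".

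Two other statements bear on the carrier count. Section 9.1 assumes that about 30% of all participants carry the protective allele. The background text before the primary hypothesis reports: "Between 31.7%-47.2% of control participants possessed at least one protective alleles".

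Section 9.2 names the model terms: allele presence or absence, time, their interaction, and the baseline value as covariate. It treats ancestry through analyses within each ancestral subgroup and names no allele-by-ancestry term.

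**The concern.** Two consecutive sentences do not agree. If 14 to 16 of 50 are carriers, the possible splits run from 14 vs 36 to 16 vs 34. The split labelled smallest is the one with the most carriers, and so the most favourable for power. The power figure is worded as a floor, but it was calculated at the top of the range.

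The closing sentence then extends the conclusion to pooled factorial analyses without saying which contrast is meant. A pooled main effect uses all 100 participants and has more power than a subgroup comparison. An interaction is a difference of two differences and has much less. The word "therefore" is sound for the first and not for the second.

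What is at stake is how null secondary results are read. The design recruits equal numbers by ancestry, so readers will look for a difference between ancestral groups. They could take this paragraph as assurance that such a difference was adequately tested.

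**Working it through.** **Inputs, all from protocol section 9.1:** difference d = 0.03 mmol/l; SD = 0.03 mmol/l in both allele groups; two-sided 5%; 50 per ancestry; 14 to 16 carriers per ancestry.

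**Method.** For c carriers and 50 − c non-carriers, SE = SD × √(1/c + 1/(50 − c)). Normal-approximation power is Φ(d/SE − 1.960). The t-test power uses the noncentral t distribution with 48 degrees of freedom, noncentrality d/SE and critical value 2.011.

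**Step 1: the protocol's own figure, 16 vs 34.** SE = 0.03 × √(1/16 + 1/34) = 0.00910, so d/SE = 3.298. Power is Φ(1.338) = 91.0% (normal) or 89.8% (t). The stated figure reproduces, but exceeds 90% only by the normal approximation.

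**Step 2: the rest of the stated range.**

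| Carriers vs non-carriers | d/SE | Power, normal | Power, t |
|---|---|---|---|
| 16 vs 34 | 3.298 | 91.0% | 89.8% |
| 15 vs 35 | 3.240 | 90.0% | 88.8% |
| 14 vs 36 | 3.175 | 88.8% | 87.5% |

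At 14 vs 36 neither method reaches 90%. The shortfall is 90 − 88.8 = 1.2 points or 90 − 87.5 = 2.5 points.

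**Step 3: the background range.** 0.317 × 50 = 15.85 and 0.472 × 50 = 23.6, or about 16 to 24 carriers per 50. On this range 16 vs 34 is the smallest split, and power at 24 vs 26 is 94.2% (normal) or 93.3% (t). The label would then be right and the 14-16 estimate wrong. The 30% assumption gives 0.30 × 50 = 15, inside 14-16 but just below the background range.

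**Step 4: pooled main effect of 0.03 mmol/l.** With 15 carriers per ancestry the pooled comparison is 30 vs 70: SE = 0.03 × √(1/30 + 1/70) = 0.00655, d/SE = 4.58, power 99.5% (t). With 14 or 16 per ancestry it is 99.4% or 99.6%.

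**Step 5: allele-by-ancestry interaction of 0.03 mmol/l.** With c carriers in each ancestry, SE = 0.03 × √(2/c + 2/(50 − c)), which is √2 times the subgroup SE; 96 degrees of freedom for the t calculation.

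| Carriers per ancestry | SE | Power, normal | Power, t |
|---|---|---|---|
| 14 | 0.01336 | 61.2% | 60.4% |
| 15 | 0.01309 | 63.0% | 62.1% |
| 16 | 0.01286 | 64.5% | 63.7% |

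**The case against.** The strongest reply is that little turns on this. The power quoted for 16 vs 34 reproduces, and the gap at 14 vs 36 is smaller than the rounding in the inputs. The SD is given to two decimals; with 0.029 mmol/l, 14 vs 36 gives 90.7% (normal) or 89.6% (t). That stands as a statement about size: the design is not underpowered in any practical sense. It does not reconcile the two sentences.

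A second reply is that the slip may lie in the 14-16 estimate and not in the label, since the background range makes 16 the minimum. That also stands. The documents do not show which statement is in error.

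Two stronger readings are tempting. A reader might infer that the protocol claims over 90% power for an allele-by-ancestry interaction and is badly wrong. The text does not support this: it names no such contrast, it says adequately powered and not over 90%, and the model in section 9.2 has no ancestry interaction. Read as a pooled main effect, the sentence is correct. A reader might also infer that it promises power for the key secondary *ABCG2* analysis. Section 9.1 states no power for *ABCG2* and gives no 141K carrier frequency, so any figure would rest on assumed carrier counts.

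**Conclusion.** The point holds in a limited form. Section 9.1 contradicts itself on the smallest subgroup comparison, and power in excess of 90% is not delivered at the smallest split on its own range. The shortfall is about 1 to 2.5 points at 14 vs 36, given the protocol's SD and difference of 0.03 mmol/l each and exactly 14 carriers.

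The factorial sentence is too broad, not false: right for a pooled main effect (over 99%), and unsupported if it is meant to include an allele-by-ancestry interaction (about 60-65% with 14 to 16 carriers per ancestry). The power statements at issue concern secondary analyses; the primary comparison is not affected by this point.

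**What to change.** In protocol section 9.1, do one of the following:

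- keep 14-16 carriers and give the smallest comparison as 14 vs 36, with about 88% power for 0.03 mmol/l; or
- correct the 14-16 estimate so that it agrees with the 31.7%-47.2% range in the background (about 16 to 24 per 50), keep 16 vs 34 as the smallest comparison, and give its power as about 90%. The 30% assumption for the whole sample should then be checked against the same source.

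Limit the last sentence to pooled main effects of the allele, with over 99% power for 0.03 mmol/l. If an allele-by-ancestry interaction is intended, say so and state that 0.03 mmol/l has only about 60-65% power with 14 to 16 carriers per ancestry.

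The cost is a few reworded sentences and slightly less favourable stated figures. No extra participants are needed and the analysis does not change.

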Whilst the primary analysis will be performed on the change from baseline, no adequate estimate of the variability of this is available and so the conservative approach of modelling the difference between groups at a single time point was chosen to validate the sample size. Removing between patient variability by using the change from baseline as the dependent variable is likely to offer increased power which should more than offset the very small number of samples which may not be adequately genotyped. Sample size calculations were performed using PASS 2002 (Hintze, J (2006) Kaysville, Utah).

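### The power reserve that Section 9.1 credits to analysing change from baseline is already inside its SD of 0.03, and the stated inputs give about 86% power, not 90%

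*Protocol*

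**What the plan says.** All of this stands in Protocol Section 9.1.

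- Basis of the calculation: "Sample size calculations have been based on the variability of change in serum urate at each time point in our previous study" (the fructose study), together with an analysis of inosine in Parkinson's disease.
- The SD: "The variability in the change in serum urate to fructose load [13] was consistent within groups with and without protective alleles across all time points", given as 0.03 mmol/l.
- The power claim: for 30 carriers of the protective allele against 70 non-carriers, power is put at 90%, two-sided at 5%. The target is worded on the change scale: "to detect a difference in the change in serum urate between these groups of at least 0.02mmol/l".
- The closing paragraph says the primary analysis will use change from baseline, but that "no adequate estimate of the variability of this is available". It therefore models the group difference at a single time point and calls that conservative.
- It adds: "Removing between patient variability by using the change from baseline as the dependent variable is likely to offer increased power", and expects this to more than cover the few samples that fail genotyping.

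Section 9.2 plans a repeated-measures mixed model on change from baseline, with the baseline value as covariate.

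**The concern.** The two parts of Section 9.1 do not fit together. The first gives an SD of change and sets its targets on the change scale. The second says that no usable SD of change exists, and treats the move to change as a gain still to come. If 0.03 is an SD of change, variation between people in their urate level has already been subtracted out, and subtracting it again gains nothing.

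This matters because the supposed gain is the only allowance for lost samples. Genotype defines the comparison groups, so a participant without a genotype cannot enter the primary comparison. The figure of 100 is both the number to be recruited and the number in the power calculation (70 + 30), with no inflation. The power sentence therefore has no stated margin, and its own inputs do not reach 90%.

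**Working it through.** **Inputs (Protocol Section 9.1).** SD of change s = 0.03 mmol/l; difference in change d = 0.02 mmol/l; groups 70 and 30; two-sided 5%; stated power 90%.

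**1. Which scale is 0.03 on?** The basis of the calculation, the SD and the detectable differences are all expressed as change. The only other urate SD in the protocol, 0.07 mmol/L in Section 7, is also the SD of an increase. No SD of a urate level is given anywhere.

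**2. The plan's own figure.**

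Standard error = s × √(1/70 + 1/30) = 0.03 × 0.2182 = 0.006547.

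Noncentrality = d / SE = 0.02 / 0.006547 = 3.055.

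- Normal approximation: Φ(3.055 − 1.960) = 86.3%.
- Noncentral t, 98 df, critical value 1.984: 85.7%.

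The stated 90% is not reproduced. At a 70:30 split, 90% would need about 113 (normal) to 115 (t) genotyped participants.

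**3. Could rounding explain it?** By the t calculation, 90% follows from an SD of about 0.0280 or a difference of about 0.0214. These round to 0.03 and 0.02, so rounding is possible. It would put power at 90% with all 100 genotyped, leaving nothing over for loss.

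**4. The subgroup figure.** For 16 vs 34 and a difference of 0.03 mmol/l, using 0.03 directly as the SD gives 91.0% (normal) or 89.8% (t). The protocol says more than 90%. The near match is what one expects if 0.03 went in as the SD of change.

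**5. Effect of genotyping loss.** The protocol gives no rate, so these are assumptions, with losses taken in proportion from both groups (noncentral t):

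| Assumed loss | Power | Cost of the loss |
|---|---|---|
| 0% | 85.7% | – |
| 1% | 85.3% | 0.4 points |
| 2% | 84.9% | 0.7 points |
| 5% | 83.8% | 1.8 points |

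**6. What the Section 9.2 model could add.** Starting from a 5% loss, with assumed correlations:

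- Baseline covariate, correlation r with change: the SD becomes 0.03 × √(1 − r²). For r = 0.3, 0.4, 0.5, power is 87.1%, 89.5%, 92.5%.
- Average of the five post-dose times, correlation ρ between times: the SD becomes 0.03 × √((1 + 4ρ)/5). For ρ = 0.9, 0.8, 0.7, power is 86.7%, 89.5%, 92.2%. This holds the average difference at 0.02.

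Both gains come from sources other than subtracting baseline.

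**The case against.** **Conservatism.** A reader might infer that the calculation is not conservative at all. The text does not support that. The word describes modelling one time point, not the choice between level and change. For the same difference and SD, an unadjusted single-time-point test is normally conservative against a repeated-measures model with a baseline covariate. This part of the objection stands. One limit is that if the genotype effect grows over time, averaging would also dilute the difference.

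**Whether any reserve exists.** A reader might also infer that the trial has no reserve, or that its true power is below 86%. That is not shown. Under the assumed correlations above, the planned model gives about 87% to 93% even after a 5% loss. What fails is only the reserve that Section 9.1 names, because it attributes the gain to using change from baseline.

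**The missing estimate.** The remark that no estimate is available may mean none for change after inosine, or none for change over all time points. That would soften the contradiction, since the 0.03 comes from a fructose load. It does not rescue the sentence about increased power.

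**0.03 as an SD of urate level.** This contradicts the labels in the same section. If it were so, the baseline covariate would bring a gain at any non-zero correlation, so it would be wrong to object that change helps only when the correlation exceeds 0.5.

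**Size.** Most of the gap to 90% is the power figure itself, which rounding may explain. Loss alone costs about 0.4 to 2 points at 1% to 5%.

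**Conclusion.** The point holds in a limited form. Section 9.1 counts one gain twice: subtracting baseline is already reflected in the 0.03, so it cannot also offset ungenotyped samples. On the inputs as printed, power for 0.02 mmol/l at 70 vs 30 is about 86% (85.7% by noncentral t), not 90%. With assumed losses of 1%, 2% and 5% it is about 85%, 85% and 84%.

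These figures rest on 0.03 being the SD of change, as the protocol labels it, on unrounded inputs, and on a single-time-point, unadjusted comparison. They describe the stated calculation, not the power of the Section 9.2 model, which may well be higher. The defect is a wrong statement in the sample size justification. It does not show that the trial is too small.

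**What to change.** Reconcile the paragraphs of Section 9.1:

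- State that 0.03 mmol/l is the SD of change at one time point, taken from the fructose study, and say precisely which estimate is unavailable (for example, change after acute inosine).
- Delete the claim that using change from baseline brings extra power that offsets lost samples.
- Restate the power as about 86% with all 100 genotyped, or give the unrounded SD and difference that yield 90%.
- Add a net power figure for a stated genotyping loss, labelled as an assumption.
- Keep the word conservative only if it is tied to the single-time-point, unadjusted calculation.
- If a reserve is still claimed, attribute it to the baseline covariate and repeated measures of Section 9.2 and state the assumed correlations.

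The cost is a few sentences and a slightly lower stated power. The endpoint, the analysis and the recruitment target need not change.

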### **9.2. Statistical Methods**

Data will be presented as mean (SD) or median (IQR) for descriptive purposes. Measures of effect will be presented with the appropriate 95% confidence interval. The primary analysis will be a comparison of the hyperuricaemic response to an inosine challenge in the entire group (n=100), based on the presence or absence of the *rs11942223* protective allele. Secondary and exploratory analyses will be comparison of the hyperuricaemic response to an inosine challenge based on subgroup analysis (within each ancestral subgroup), and based on other clinical features, such as age, sex and BMI in the entire group.

A key secondary analysis is the effect of the *ABCG2 Q141K* risk variant on the serum urate and FEUA response to an inosine challenge.

Data will be analysed using a mixed models approach to repeated measures where the dependent variable, change from baseline, will be examined in an analysis of covariance. Main effects of allele presence/absence, time and their interaction will be constructed and the baseline value of the dependent variable will be included as covariate. Significant group effects will be explored using the method of Tukey to preserve an overall 5% significance level. All analyses will be performed using SAS (SAS Institute Inc v 9.4) on an intention to treat basis. All tests will be two-tailed.

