### **5. STUDY ENDPOINTS**

#### **5.1. Primary Endpoint**

Change from baseline in serum urate concentration over 3 hours following an inosine challenge

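### Section 9.2 does not say which model term decides the primary hypothesis, and its Tukey step does not secure the overall 5% level claimed for it

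*Protocol*

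**What the plan says.** - **Endpoint (section 5.1):** "Change from baseline in serum urate concentration over 3 hours following an inosine challenge". No time point or summary over time is given. Sections 6.3 to 6.5 schedule post-dose blood samples at 15, 30, 60, 120 and 180 minutes.
- **Primary comparison (section 9.2):** carriers against non-carriers of the *SLC2A9* protective allele in all 100 participants. The method is a repeated-measures mixed model of change from baseline, with baseline as covariate: "Main effects of allele presence/absence, time and their interaction will be constructed".
- **Follow-up (section 9.2):** "Significant group effects will be explored using the method of Tukey to preserve an overall 5% significance level".
- **Overall power (section 9.1):** "With 70 participants without the protective allele and 30 with the protective allele", the study is said to have power of "90% at the 5% significance level for a two tailed test". The effect size behind this figure is given as "a difference in the change in serum urate between these groups of at least 0.02mmol/l". The SD is 0.03 mmol/L. No time point is named here.
- **Subgroup power (section 9.1):** within an ancestry group, a "difference in the change in serum urate 180 minutes after an oral inosine challenge of at least 0.03 mmol/l". This is the only place in section 9.1 that names 180 minutes.
- **Basis of the calculation (section 9.1):** the protocol discloses that "modelling the difference between groups at a single time point was chosen to validate the sample size", and describes this as conservative.

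**The concern.** The planned model offers at least three answers to the primary question: the allele effect averaged over five times, the allele-by-time interaction, and the genotype contrast at a particular time. They are different hypotheses with different power, and the protocol does not choose among them. If the choice is left until results are seen, the 5% level is not protected.

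The Tukey sentence is the only stated safeguard, and it does not address that choice. It also attaches follow-up to a significant group effect. Read literally, a difference that emerges late and shows mainly in the interaction might never be examined.

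The sample size was checked at one time point. Whether that is cautious for the averaged effect depends on how the genotype difference develops over 3 hours, which the protocol does not state.

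**Working it through.** **Inputs from section 9.1:** 70 vs 30 participants, difference 0.02 mmol/L, SD 0.03 at each time, two-sided 5%. **Assumed, because not given:** within-person correlation ρ of 0.3 to 0.9, equal between all pairs of times, and three illustrative time profiles. The baseline covariate is not modelled.

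**1. The plan's own figure.** SE = 0.03 × √(1/70 + 1/30) = 0.00655, and 0.02 / 0.00655 = 3.055. Power is 86.3% (normal) or 85.7% (noncentral t, 98 df), against 90% stated. The difference detectable with 90% power is 0.0212 to 0.0214, which rounds to 0.02, so rounding may explain the gap. The single-time benchmark below is 86%.

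**2. Power of the model terms.** The SD of the five-time mean is 0.03 × √((1 + 4ρ)/5), that is 0.0199 / 0.0232 / 0.0262 / 0.0288 at ρ = 0.3 / 0.5 / 0.7 / 0.9. For a linear rise to 180 minutes the mean time is (15 + 30 + 60 + 120 + 180)/5 = 81 minutes, so the average difference is 0.02 × 81/180 = 0.009. If the difference exists only at 180 minutes, the average is 0.02/5 = 0.004. The interaction is a 4 and 392 df F test with noncentrality 21 × Σ(dⱼ − d̄)² / (0.03² × (1 − ρ)), where 21 = 70 × 30/100.

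| Genotype difference | Average | Main-effect power, ρ = 0.3 / 0.5 / 0.7 / 0.9 | Interaction power, same ρ |
|---|---|---|---|
| Constant 0.02 | 0.020 | 99.5 / 97 / 93 / 88% | 5% throughout |
| Linear to 0.02 at 180 min | 0.009 | 54 / 42 / 35 / 29% | 58 / 75 / 94 / over 99% |
| 0.02 at 180 min only | 0.004 | 15 / 12 / 11 / 10% | 74 / 89 / 99 / over 99% |

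**3. Error rate if either term counted.** For two independent tests it is 1 − 0.95² = 9.75%. In 20,000 simulated null trials it was 9.4% (ρ = 0.5) and 9.5% (ρ = 0.8).

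**4. Tukey, two readings.**
- *Allele factor, two levels:* the studentized-range critical value divided by √2 is 1.984 on 98 df, identical to the unadjusted t. Nothing is adjusted.
- *All 2 × 5 = 10 cells:* 10 × 9/2 = 45 pairs. Of these, 5 compare genotypes at the same time, 20 compare times within a genotype, and 20 compare different genotypes at different times. The critical t is 3.18 to 3.24 (392 to 98 df), the per-comparison level is about 0.0016, and power for 0.02 at one time is 43–45%.

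**5. Adjusting over the five genotype contrasts only.** The first Holm step uses 0.05/5 = 0.01, critical t 2.63, power 67%. A simulation-based (multivariate t, 98 df) critical value runs from 2.60 at ρ = 0.3 to 2.31 at ρ = 0.9, with power 68% to 77%.

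**The case against.** **180 minutes as the powered contrast.** A reader might infer that the primary comparison was powered at 180 minutes and is then tested by something else. The text does not support this: 180 minutes appears only in the ancestry-subgroup sentence, and the overall calculation names no time. Nor does it follow that 180 minutes should become the primary time point. That would narrow an endpoint defined over 3 hours, and could lose power if the difference peaks earlier.

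**Disclosure.** The single-time basis is openly stated as a simplification, and for a constant difference the word conservative is right (88–99.5% against 86%). This stands. What is missing is any statement that the difference is expected to be constant.

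**Dilution of the main effect.** A reader might infer that the planned analysis is badly underpowered. That is not shown. The low figures depend on assumed late profiles, and under those profiles the interaction in the same model has 58% to over 99% power. This makes it more important to say which term decides.

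**Error rate.** The protocol does not say that either term suffices, so 9.5% is conditional on that reading. If follow-up is instead strictly gated on the group effect, the interaction alone cannot deliver success and the problem becomes a missed late difference. These are alternative readings and do not add up. Nor does the protocol plan unadjusted tests at each time.

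**Tukey.** Two groups need no adjustment for a single comparison, and over 10 cells Tukey does control error within that family. Its 43–45% power belongs to follow-up comparisons, not to the primary test. All of this stands, but neither reading covers the choice among main effect, interaction and time point.

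**Unseen SAP.** Details of post-hoc testing may properly sit there. The deciding primary contrast, and a protocol sentence that claims an overall 5% level, belong in the protocol.

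**Conclusion.** The point holds as an unfixed primary test combined with a multiplicity step that does not do what is claimed for it. Sections 5.1 and 9.2 leave open which term decides the primary hypothesis. The consequence is an error rate of about 9.5% if either term were accepted, or a possible missed late difference if follow-up is gated on the group effect. Tukey either adjusts nothing or spends the error rate on 45 pairs to examine 5, at about 45% power per time point where 67–77% is available at the same overall level.

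The conservative label in section 9.1 is unproven rather than wrong: it holds for a roughly constant genotype difference and fails for the averaged effect under late build-up. The power ranges rest on the assumed correlations and profiles. The two-group Tukey result and the count of pairs rest on no assumption.

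**What to change.** 1. In sections 5.1 and 9.2, name one deciding contrast from the planned mixed model, tested at two-sided 5%. It can be the allele effect averaged over 3 hours or the allele contrast at one stated time, chosen by the sponsor before analysis. Make the remaining terms secondary.
2. In section 9.1, state the power for that contrast with the assumed time profile and correlation, or drop the word conservative.
3. Replace the Tukey sentence by a Holm or simulation-based adjustment over the five between-genotype time-point contrasts, not conditional on a significant main effect.

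The cost is wording in three sections and one estimate or adjustment statement in the analysis program. Visits, samples and recruitment do not change. The contrasts not chosen lose primary status.

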### **PRIMARY HYPOTHESIS**

That individuals possessing at least one protective allele at *SLC2A9 rs11942223* have a lower hyperuricaemic response to an inosine challenge.

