### **KEY SECONDARY HYPOTHESIS**

That individuals possessing at least one *ABCG2 141K* variant have a higher hyperuricaemic response to an inosine challenge.

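### Section 9.2 models SLC2A9 and ABCG2 one at a time; putting both genotypes in one model would be a modest, nearly free gain in precision (an optional improvement, not an error)

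*Protocol*

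**What the plan says.** The primary hypothesis is that carriers of the SLC2A9 rs11942223 protective allele "have a lower hyperuricaemic response to an inosine challenge". The key secondary hypothesis is that carriers of the ABCG2 141K "variant have a higher hyperuricaemic response to an inosine challenge". The background adds that, in the team's earlier fructose studies, variants of both genes influenced the change in serum urate. It also describes both genes as strongly associated with serum urate. Section 8.1 takes DNA for both genes from the baseline blood sample.

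Section 9.2 compares the whole group by presence or absence of the rs11942223 allele. It lists separately, as a key secondary analysis, the effect of the ABCG2 "risk variant on the serum urate and FEUA response to an inosine challenge". It describes one model: "Main effects of allele presence/absence, time and their interaction will be constructed", with the baseline value of the dependent variable as covariate. No term for the other gene is named.

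Section 9.1 refers once to secondary analyses that are pooled and factorial, but does not name the factors.

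**The concern.** Each gene is, by the protocol's own hypotheses, a predictor of the outcome in the other gene's test. A known predictor left out of a linear model adds to the residual variance and widens the confidence interval. Genotype is fixed before dosing and both genotypes are already measured, so the usual reasons for leaving a predictor out (post-treatment status, cost, missing data on a large scale) do not apply.

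The baseline covariate raises a second, smaller matter. If both genes also shift baseline urate, conditioning on baseline makes two otherwise independent genotypes associated within the model. Part of the omitted gene's effect then moves into the estimate for the gene that is kept.

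At stake is some precision for the two named hypotheses.

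**Working it through.** **Inputs from the protocol (section 9.1).** Group sizes: "With 70 participants without the protective allele and 30 with the protective allele". Target: "to detect a difference in the change in serum urate between these groups of at least 0.02mmol/l". Power and level: "90% at the 5% significance level for a two tailed test". Spread: the change in urate "was consistent within groups with and without protective alleles across all time points (SD 0.03 mmol/l"), taken from the fructose study.

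**Inputs assumed.** The protocol gives neither an ABCG2 effect *e* nor a 141K carrier share *p*. I use *e* = 0.01 to 0.03 mmol/L and *p* = 15 to 45%, with the genes independent.

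**Step 1: the plan's own figure.** SE = 0.03 × √(1/70 + 1/30) = 0.00655. Two-sided power for 0.02 mmol/L is 86.3% (normal) or 85.7% (noncentral t, 98 df), against the stated 90%. A difference of 0.0212 to 0.0214 would give 90%, and that rounds to 0.02. This gap has nothing to do with single-gene modelling. The 85.7% serves here only as the reference value.

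**Step 2: ABCG2 in the residual of the SLC2A9 test.** Variance due to ABCG2 = p(1 − p)e². Residual SD with ABCG2 in the model = √(0.0009 − p(1 − p)e²). At e = 0.02, p = 0.3: 0.21 × 0.0004 = 0.000084, which is 9.3% of 0.0009. Residual SD = 0.0286, and the SE falls from 0.00655 to 0.00623 (about 5%).

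| Assumed ABCG2 effect (mmol/L) | Primary power with ABCG2 in the model, 15 to 45% carriers | At 30% carriers |
|---|---|---|
| 0.01 | 86.1 to 86.6% | 86.5% |
| 0.02 | 87.6 to 89.4% | 88.8% |
| 0.03 | 89.9 to 93.7% | 92.6% |

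The reference without ABCG2 is 85.7%. These figures treat 0.03 as including the ABCG2 variation, since section 9.1 mentions no adjustment for it. If 0.03 were instead net of ABCG2, the comparison at e = 0.02, p = 0.3 would be 82.5% without and 85.7% with the second gene, again a gain of about 3 points.

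**Step 3: validity.** In 40,000 simulated trials (e = 0.02, p = 0.3, one change value per person, no baseline covariate), type I error was 5.0% without and 4.9% with ABCG2. The mean estimate was −0.0201 in both models for a true −0.02. Power was 85.8% and 88.8%.

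**Step 4: the baseline covariate.** Suppose the SLC2A9 allele lowers baseline urate by *b*, 141K raises it by *b*, and the remaining baseline SD is *s*. Leaving ABCG2 out then moves the SLC2A9 coefficient towards zero by

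e × b²p(1 − p) / [b²p(1 − p) + s²].

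With e = 0.02 and p = 0.3:
- b = 0.02, s = 0.07: 0.02 × 0.000084 / (0.000084 + 0.0049) = 0.0003 mmol/L.
- b = 0.03, s = 0.05: 0.02 × 0.000189 / (0.000189 + 0.0025) = 0.0014 mmol/L.

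That is 2 to 7% of the 0.02 target. A simulation of the baseline-adjusted model with b = 0.03 gave a mean of −0.0191 for a true −0.02, and power of 80.6% without against 86.9% with ABCG2. With no SLC2A9 effect, a shift of 0.001 against an SE of about 0.0065 is 0.15 SE. The size becomes Φ(−1.81) + Φ(−2.11) ≈ 5.3%, so the test stays close to its level.

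**Step 5: SLC2A9 in the residual of the ABCG2 test.** Here the protocol's own inputs serve. Because 0.03 is a spread within SLC2A9 groups, a 0.02 effect in 30% of participants adds 0.3 × 0.7 × 0.02² = 0.000084 when SLC2A9 is left out. The SD becomes √0.000984 = 0.0314. Including SLC2A9 shrinks the SE by a factor of √(0.0009/0.000984) = 0.956, about 4%.

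**The case against.** The best case against is that nothing here is wrong. The section 9.2 analysis tests the primary hypothesis as worded, carriers against non-carriers of one allele. With independent genes it is unbiased apart from the small baseline effect in step 4. Further covariates may sit in a SAP that is not shown, and the factorial secondary analyses of section 9.1 neither state nor exclude a two-gene model. The gain rests on assumed ABCG2 inputs, is under 1 point at effect 0.01, and passes 90% only with an effect near 0.03, half as large again as the SLC2A9 target. Baseline urate might also absorb part of the ABCG2 effect. Adjustment is not wholly free, because section 9.1 expects a few samples to fail genotyping.

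Most of this stands, and it is why the point is optional. Two parts do not. A factorial analysis classed as secondary does not change the primary test, whatever its factors. And in the simulation with both genes shifting baseline, the baseline covariate did not remove the gain.

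A reader might be tempted by stronger readings that the documents do not support:

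- **Chance imbalance in 141K carriage could offset or mimic the primary effect.** At e = 0.02, p = 0.3 that imbalance shifts the contrast with an SD of √(0.21 × (1/30 + 1/70)) × 0.02 = 0.002 mmol/L. This is random and already inside the unadjusted SE. Counting it beside the power loss counts the same variance twice.
- **Opposite directions make the omission worse.** The residual variance depends on e², so the sign is irrelevant there. Direction matters only for which way the small baseline-related shift goes.
- **Single-gene modelling explains the shortfall from 90% power.** It does not. The 0.03 SD plausibly already contains the ABCG2 variation.
- **Pooling ancestries confounds the two genes.** This needs carrier shares that differ by ancestry for both genes. Under assumed shares the shift is about 0.0002 to 0.0013 mmol/L, small against 0.02.

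**Conclusion.** The point holds as an optional efficiency improvement. The stated model omits a predictor that the protocol itself names and measures. With independent genes the tests remain valid to a close approximation. The cost of the omission is a standard error about 5% larger than necessary at an ABCG2 effect of 0.02 with 30% carriers, or about 3 points of primary power (85.7% against 88.8%). Across the assumed range the adjusted power is 86 to 94%. If both genes also shift baseline urate by 0.02 to 0.03 mmol/L, with a remaining baseline SD of 0.05 to 0.07, the SLC2A9 estimate is also attenuated by 2 to 7% of the target.

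These sizes rest on assumed ABCG2 effects, carrier shares and baseline effects. The power figures in the table are for a single time point, as in section 9.1, and not for the full repeated-measures model. The documents support no conclusion that the primary analysis is invalid or would mislead.

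**What to change.** In section 9.2 (or the SAP), specify one model per endpoint containing the SLC2A9 protective-allele indicator, the ABCG2 141K indicator, time, each indicator's interaction with time, and the baseline value. Read the primary hypothesis from the SLC2A9 term and the key secondary from the ABCG2 term. Report the single-gene estimates as sensitivity analyses. Name the factors of the factorial analyses mentioned in section 9.1.

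State how a participant with only one usable genotype is kept, for example with a missing-genotype category, so that the joint model does not drop people whose SLC2A9 status is known.

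The cost is wording plus up to 5 degrees of freedom for the second gene (1 for the indicator and 4 for its interaction over five post-dose times). No new samples, visits or participants are needed.
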